**Primary outcome measures:**

- Fasting insulin level [ mIU/L]
- HOMA-IR
- Six minute walk test
- Quality of life by WHOQOL-BREF

**Secondary outcome measures:**

- Body composition analysis
- Fasting blood sugar [mg/dL]
- HbA1c
- Physical activity using GPAQ questionnaire.

**Data analyses:**

- Data will be analysed using SPSS version 15
- Paired t test will be used to analyse within the groups & independent t test is used between the groups
- Descriptive statistics will be used to analyse the age, GPAQ & body composition
- Level of significance will be set at p<0.05

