**Investigator:**

Physiotherapist pursuing his structured Ph.D. program.

- **Sample size:** Sample size calculated based on the ***Fasting insulin level*** outcome measure

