**N= 2[z_1-α/2_ + z_1-β_] ^2^** $\boldsymbol{\times}$**σ^2^**

**(d) ^2^**

***z_1-α/2_ = Level of significance z_1-α/2_ = 1.96***

***z_1-β_ = Power z_1-β =_ 0.84***

***σ = Standard deviation σ=8.26***

***d = Clinical significance difference d = 2***

With a drop out of 20%, the final sample size will be **120** in each group

**Sampling method:** Purposive Sampling

**Randomization:** Block randomization

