**Source: *Acsm Guidelines for Exercise Testing and Prescription 9^th^ edition***

**Consort of Phase – I**

- Permission will be sought from Institutional Research Committee and Institutional Ethical Committee and trial will be registered under CTRI. All participants will be screened for insulin resistance Informed consent will be obtained from the participants who are willing to take part in the study
- Participants will be clinically and biochemically evaluated for following outcomes

**Primary outcome**: Fasting Insulin Level, HOMA-IR, WHOQOL- BREF, Six minute walk test

**Secondary outcome:** Body composition analysis, Fasting blood sugar, GPAQ, HbA1c.

The participants will be randomized into study group and control group (Block Randomization)

Control Group

Study group

No structured exercise program will be given to the control group participants

Study group participants will be given a set of exercise programs along with the standard care.

Standard hospital care will be advised to the participants

Adherence to exercise will assessed by telephonic call, log book and check list will be given to all the participants

Participants will be asked to continue routine work

After 6 weeks progression of exercise program will be prescribed by the principal investigator

Reassessment of all outcome measures will be done at 3 month

Reassessment of all outcome measures will be done at 3 month

Data will be analyzed

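### The only planned between-group comparison is an unadjusted independent t test; it is valid, but it is less precise than ANCOVA using the baseline values the trial already collects

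*Protocol*

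**What the plan says.** The Data analyses section of the protocol names the comparative methods in one line: "Paired t test will be used to analyse within the groups & independent t test is used between the groups". It adds "Level of significance will be set at p<0.05" and assigns age, GPAQ and body composition to descriptive statistics. It does not say whether the independent t test is applied to the 3-month value or to the change from baseline. No ANCOVA or other baseline adjustment is mentioned in the protocol.

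The flow under Consort of Phase – I shows that baseline values will exist. Ahead of the randomisation step it says "Participants will be clinically and biochemically evaluated for following outcomes", followed by the primary and secondary outcomes. For both groups it then says "Reassessment of all outcome measures will be done at 3 month".

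The sample size section, built on fasting insulin, gives "Level of significance z_1-α/2_ = 1.96", "Standard deviation σ=8.26" and "Clinical significance difference d = 2", and arrives at 120 per group after 20% dropout. It does not say whether 8.26 is the SD of a single measurement or of a change.

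**The concern.** Each outcome has its own baseline value, usually the best single predictor of the value at 3 months. The only use of baseline that the plan states outright is the within-group paired t test, and that test does not compare the randomised groups. In the between-group test, baseline is either ignored (t test on 3-month values) or subtracted in full (t test on change). Full subtraction is noisier than ignoring baseline when the correlation between the two measurements is below 0.5.

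What is at stake is precision: wider confidence intervals and lower power than the same participants and assays could give. The protocol is not silent here. It names a specific method, and a later analysis plan that followed it would carry the loss forward.

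**Working it through.** **Inputs from the protocol.** SD 8.26, difference d = 2 and two-sided alpha 0.05 (z = 1.96) come from the sample size section. It also gives 120 per group with 20% dropout, so 120 × 0.80 = 96 evaluable per group.

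**Assumptions.** The correlation r between baseline and 3 months is not given; 0.3 to 0.8 is shown. Whether 8.26 is the SD of one measurement or of change is not given; both are shown. Baseline and 3-month SDs are taken as equal. The one degree of freedom that ANCOVA spends on the covariate is ignored.

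**The plan's own figure.** The protocol's formula gives 2 × (1.96 + 0.84)² × 8.26² / 2² = 267.45, so 268 per group, and 268/0.80 = 335 after dropout. It does not give 120. That is a separate problem; it enters here only because 96 evaluable is what the stated 120 would leave.

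**Unadjusted test.** SE = 8.26 × √(2/96) = 1.19, so d/SE = 2/1.19 = 1.68. Power from the non-central t distribution with 190 degrees of freedom is 38.6%.

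**Variance factors, with σ the single-measurement SD.**
- t test on 3-month values: σ²
- t test on change: 2(1 - r)σ²
- ANCOVA: (1 - r²)σ²

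ANCOVA against 3-month values is therefore 1 - r². ANCOVA against change is (1 - r²)/[2(1 - r)] = (1 + r)/2. The first is below 1 for any non-zero r and the second for any r below 1, so the direction does not depend on which scale the t test uses.

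**Reading A: 8.26 is the SD of a single measurement.** The ANCOVA SD is 8.26 × √(1 - r²); the change-score SD is 8.26 × √(2 - 2r).

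| r | 1 - r² | ANCOVA power | t test on 3-month value | t test on change |
|---|---|---|---|---|
| 0.3 | 0.91 | 41.7% | 38.6% | 29.2% |
| 0.5 | 0.75 | 48.7% | 38.6% | 38.6% |
| 0.6 | 0.64 | 55.0% | 38.6% | 46.3% |
| 0.7 | 0.51 | 64.7% | 38.6% | 57.7% |
| 0.8 | 0.36 | 79.4% | 38.6% | 75.1% |

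**Reading B: 8.26 is the SD of change.** The ANCOVA SD is 8.26 × √((1 + r)/2).

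| r | (1 + r)/2 | ANCOVA power | t test on change |
|---|---|---|---|
| 0.3 | 0.65 | 54.4% | 38.6% |
| 0.5 | 0.75 | 48.7% | 38.6% |
| 0.6 | 0.80 | 46.3% | 38.6% |
| 0.7 | 0.85 | 44.1% | 38.6% |
| 0.8 | 0.90 | 42.1% | 38.6% |

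The gain grows with r under reading A and shrinks with r under reading B.

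**Chance imbalance.** With 96 per group under reading A, the baseline difference between groups has SE 1.19, and r times that difference is passed on to the 3-month comparison. One SD of this shift is 0.3 × 1.19 = 0.36 at r = 0.3, 0.60 at 0.5, 0.83 at 0.7 and 0.95 at 0.8. The probability of a shift of 2 or more in either direction is under 0.01% at r = 0.3, 0.08% at 0.5, 1.7% at 0.7 and 3.6% at 0.8.

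**The case against.** The strongest reply is that nothing here is an error. A two-sample t test in a randomised trial is unbiased and holds its type I error, and covariate adjustment is often settled in a statistical analysis plan, which is not at hand. The first part stands in full: this is a point about efficiency. The second stands only in part, because the protocol does not leave the method open; it names one.

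A second reply is that the t test may be meant for change scores, which the accompanying paired test makes plausible. Baseline would then be used, and it would be too strong to say that the plan discards it. That stands. The remaining loss is smaller when r is high: at r = 0.7 ANCOVA has 85% of the change-score variance.

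A third is that the size of the gain cannot be known from the protocol. That stands too. It rests on r and on what 8.26 measures, and the two readings of 8.26 give opposite patterns across r.

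A reader might also infer more than the documents support:
- **That the unadjusted result would be biased, or could easily be moved by as much as d = 2 through chance imbalance.** A shift of that size has probability below 4% even at r = 0.8, and the standard error of the t test already allows for chance imbalance.
- **That ANCOVA would restore the intended 80% power.** It comes close only if 8.26 is a single-measurement SD and r is about 0.8. The low starting power comes from the sample size calculation, which needs its own correction.
- **That every outcome is affected.** GPAQ and body composition are to be described only, so no between-group test is planned for them.

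**Conclusion.** The point holds as a matter of efficiency. The protocol fixes an unadjusted independent t test although baseline values are available, and in large samples ANCOVA is at least as precise on either scale the t test might use. At 96 evaluable per group and d = 2, power for fasting insulin moves from 39% to between 42% and 79% if 8.26 is a single-measurement SD, or to between 42% and 54% if it is the SD of change, for r from 0.3 to 0.8. The direction is firm. The size is uncertain, because it rests on two quantities the protocol does not give. The change is worth making because it costs almost nothing, but the planned test is not invalid without it.

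**What to change.** For the outcomes the plan would compare by t test (fasting insulin, HOMA-IR, six minute walk test, WHOQOL-BREF, fasting blood sugar and HbA1c), replace the between-group t test by ANCOVA: the 3-month value as response, randomised group as factor, and the baseline value of the same outcome as covariate. Report the adjusted mean difference with its 95% CI. Keep the within-group paired tests as description only, and leave GPAQ and body composition as they are. State also whether 8.26 is the SD of a single measurement or of change, so that the expected gain can be judged.

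The cost is one sentence in Data analyses and a clarification in the sample size section. SPSS fits the model directly, and no new data, visits or participants are needed. The mismatch between the stated 120 per group and the protocol's own inputs should be corrected separately.

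### Within-group paired t tests share the p<0.05 threshold with the between-group test, and the protocol does not say that only the between-group comparison answers the effectiveness objectives

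*Protocol*

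**What the plan says.** The Data analyses section of the protocol puts both comparisons in one sentence. It opens with "Paired t test will be used to analyse within the groups" and goes on to name an independent t test for the comparison between arms. It then gives a single threshold: "Level of significance will be set at p<0.05". Descriptive statistics are assigned there to age, GPAQ and body composition, so the paired tests fall on the inferential side. The section sets no order between the two kinds of test.

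The Objective of the Study section asks four questions, all about the effectiveness of the exercise programme (on fasting insulin, quality of life, walking distance and HbA1c). The Consort of Phase – I section describes randomisation to a study group or a control group. For the control group it notes "Standard hospital care will be advised to the participants"; the study group receives exercise on top of standard care. Both arms are reassessed at 3 months. The same section says of entry: "All participants will be screened for insulin resistance".

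**The concern.** An effectiveness objective in a randomised trial is a question about the difference between arms. A paired t test in the study arm asks something else: whether that arm changed over 3 months. Standard care, trial participation, the passage of time or selection at entry can all produce a change without any exercise effect. Comparing the two arms' paired results (significant in one, not in the other) does not test their difference either.

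Because the protocol gives the two tests the same threshold and no hierarchy, a report could quote a significant within-arm fall in answer to an effectiveness objective even when the groups do not differ, and still be following the written plan.

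**Working it through.** **Inputs from the protocol.** "Level of significance z_1-α/2_ = 1.96" (two-sided), a power term of 0.84, "Standard deviation σ=8.26", "Clinical significance difference d = 2", 20% dropout and 120 per group. Completers per arm: 120 × 0.8 = 96. The protocol does not say whether 8.26 is the SD of single values or of changes; I take it as the SD of values.

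**The plan's own figure.** 2 × (1.96 + 0.84)² × 8.26² / 2² = 267.5, so 268 per group, and 268 / 0.8 = 335 after dropout. The stated 120 does not follow from these inputs. That is a separate matter; here 120 is used as stated.

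**Assumptions.** A correlation r between baseline and 3-month values of 0.5 to 0.7, and a fall of 1.5 mIU/L in both arms that has nothing to do with exercise.

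**Step 1: paired test in the study arm, exercise effect zero.** SD of change = 8.26 × √(2 − 2r); standard error = SD of change / √96; two-sided t test on 95 degrees of freedom.

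| r | SD of change | Standard error | 1.5 / SE | P(significant fall) |
|---|---|---|---|---|
| 0.5 | 8.26 | 0.843 | 1.78 | 0.421 |
| 0.7 | 6.40 | 0.653 | 2.30 | 0.623 |

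With no common change, this probability is 2.5%.

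**Step 2: between-group test, same scenario.** The common fall cancels, so the expected difference is 0 and the test rejects in about 5% of trials, about 2.5% in favour of exercise.

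**Step 3: study arm significant, control arm not.** The arms are independent and share the same probability p, so this is p(1 − p): 0.421 × 0.579 = 0.244 and 0.623 × 0.377 = 0.235. Roughly 24% of trials would show the misleading pattern, with no exercise effect.

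**Step 4: can regression to the mean be sized?** If entry selected people above a cut-off, and the screening value were also the baseline, the expected fall is 8.26 × (1 − r) × φ(c) / (1 − Φ(c)), with c the cut-off in SD units.

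| Assumed selection | r = 0.5 | r = 0.7 | r = 0.8 |
|---|---|---|---|
| None | 0 | 0 | 0 |
| Upper 75% | 1.75 | 1.05 | 0.70 |
| Upper 50% | 3.30 | 1.98 | 1.32 |

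The range runs from 0 to beyond the target difference of 2, and the protocol does not say where in it the trial lies.

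**Step 5: what baseline adjustment gives.** Power for a difference of 2 with 96 per arm, normal approximation, standard error = SD × √(2/96), power = Φ(2/SE − 1.96).

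| Analysis | SD used | SE | Power |
|---|---|---|---|
| Final values | 8.26 | 1.192 | 39% |
| ANCOVA, r = 0.5 | 8.26 × √(1 − 0.25) = 7.15 | 1.033 | 49% |
| ANCOVA, r = 0.7 | 8.26 × √(1 − 0.49) = 5.90 | 0.851 | 65% |

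**The case against.** The strongest reply is that the valid comparison is already planned: the independent t test stands in the same sentence, and nowhere does the protocol say that a within-arm fall will count as proof. Listing the paired test first is word order, not a hierarchy. Which analysis carries the conclusion is often settled in a SAP, and any SAP here is not shown. This stands in part, and it limits the point to a missing hierarchy. It does not remove the point, because the protocol itself names an inferential test that cannot answer its objectives and gives that test equal standing.

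Three stronger readings are tempting but not supported.

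- A reader might infer from the screening statement that regression to the mean will itself produce a fall of about 2. That needs an insulin cut-off, the screening value used as baseline, and a low enough test-retest correlation. None is stated: the eligibility criteria contain no insulin or HOMA-IR threshold, and the Consort section lists the outcome evaluation after screening and consent, so baseline may be a fresh sample. With no selection the expected fall is 0.
- A reader might say that one arm alone is significant in nearly half of null trials. In the 1.5 scenario that figure, 47% to 49%, also counts trials in which only the control arm is significant; study arm only is about 24%. Under upper-half selection, exactly one arm is significant in about 2%, 20% and 40% of trials at r = 0.5, 0.7 and 0.8, because with a large common fall both arms tend to be significant.
- A reader might call a significant study-arm fall beside a non-significant group difference the likeliest result. With a true effect of 2 and no common fall, that pattern arises in about 35% to 50% of trials if final values are compared, where it is the commonest, but in about 30% if change scores are compared, where it is not. The protocol does not say which the independent t test uses.

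**Conclusion.** The point holds in limited form. The protocol plans within-group paired tests as inference, at the same threshold as the between-group test, and does not reserve the effectiveness conclusion for the randomised comparison. That rests on the text alone.

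The size is illustrative. A non-exercise fall of 1.5 mIU/L in both arms would make the study arm significant in about 42% to 62% of trials with zero exercise effect, against about 5% for the between-group test. This depends on the assumed 1.5, on r = 0.5 to 0.7, and on reading 8.26 as the SD of values. Regression to the mean is one possible source of such a fall, but the protocol does not allow its size to be derived. Nor do the documents show any intention to claim effectiveness from a within-arm result; they leave that open.

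**What to change.** In Data analyses, state that effectiveness is judged only on the between-group difference at 3 months, estimated by ANCOVA with the baseline value of the same outcome as covariate. Report within-group change as mean and SD, descriptively, with no p values offered as evidence of effectiveness.

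The baseline values are already collected, so no visit, measurement or sample-size figure changes. The adjustment also settles whether final values or changes are compared and brings the power gain shown above, although power stays below the planned 80% on the protocol's own SD and difference. The downside is only that within-arm p values can no longer be quoted.

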**Research plan schedule:**

| **Study duration** | **1^st^ year** | | | | **2^nd^ year** | | | | **3^rd^ year** | | | | |
| --- | --- | --- | --- | --- | --- | --- | --- | --- | --- | --- | --- | --- | --- |
| **Calendar years** | **2016-17** | | | | **2017-18** | | | | **2018-19** | | | | |
| **Quarterly** | **1** | **2** | **3** | **4** | **5** | **6** | **7** | **8** | **9** | **10** | **11** | **12** |  |
| **Literature review** |  |  |  |  |  |  |  |  |  |  |  |  |  |
| **1. IEC clearance & University registration** |  |  |  |  |  |  |  |  |  |  |  |  |  |
| **2. Phase-I, Randomized controlled trial** |  |  |  |  |  |  |  |  |  |  |  |  |  |
| **5. Data analysis phase-I** |  |  |  |  |  |  |  |  |  |  |  |  |  |
| **6. Reporting and submission** |  |  |  |  |  |  |  |  |  |  |  |  |  |

